## METHODS: MONITORING

4

Please refer to Appendix S1 for information on data “Monitoring”.

### Harms

4.1

Any adverse event (AE) will be documented on paper (diary). Adverse events of special interest (AESIs) as well as serious adverse events (SAEs) will also be documented in the Research Electronic Data Capture, REDCap (Vanderbilt University in Nashville, USA). In case of an AESI, caregivers will be strictly advised to contact the study site as soon as possible. SAEs have to be reported within 48 h after knowledge of the event to the principal investigator. An SAE will be defined as any AE that fulfills at least one of the following criteria: results in death; is life‐threatening; requires inpatient hospitalization (longer than 24 h) or prolongation of existing hospitalization; or results in persistent or significant disability or incapacity.

The following are considered as AESIs:
Objective immediate‐type allergic reactions within 2 hours of food exposure (either to the study product or due to exposure to other food allergens). Caregivers will be asked to call for medical help (emergency call), to document the symptoms in the subject's diary, and to call the study site before giving the next dose of the study product (Group A) in order to assess further details.Recurrent gastrointestinal symptoms/abdominal pain. Caregivers will be asked to document the symptoms in the subject's diary and to call the investigational site.Any form of new onset eczema should be reported immediately. An unscheduled site visit for visual examination and diagnosis of atopic dermatitis using modified Hanifin and Rajka criteria will be carried out according to investigators' discretion.^31^, ^32^, ^33^, ^34^ In case of a pre‐existing (at screening) or newly diagnosed atopic dermatitis, caregivers will be handed out an extra diary.

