#### Intervention description

2.3.1

Mothers of both groups will be encouraged to continue breastfeeding while weaning foods are introduced stepwise to the infant's diet. Parents will decide in advance which group they would like to join, and—depending on the child's individual development—when first complementary foods are to be introduced (Figure 1). All participants will be informed equally regarding current feeding recommendations.^17^, ^21^

All Group A participants will visit the study site at five timepoints (V1–V5). Group B participants will visit the study site at two timepoints (V1 and V5). Blood samples will be collected at V1 and V5; SPT will be performed at V5 only. Samples for microbiome analysis will be taken at indicated visits. Telephone calls are scheduled 2 weeks after V1, V2, V3, and V4 (Group A) and 2 weeks after V1 as well as one interim phone call at week 12 (Group B).

All caregivers will be encouraged to keep a weekly diary recording frequency of pre‐chewing, tolerability, and palatability of solids introduction, as well as any adverse events, concomitant medication, and diet.

V0 (collection of stools + skin swabs) and V6 (enhanced diagnostic in sensitized subjects, including oral food challenges) are optional.

V5 solo consists only of V5 (and optional V6); participants will not have been enrolled before.

Group A – “Interventional/Pre‐chewing Group”: The mother (or one other previously determined caregiver) of an eligible infant will receive a sugar‐free ground biscuit once the infant starts eating complementary foods. The biscuit is ground to ensure homogeneity of the amount of included food proteins. These amounts will be increased by a factor of five in four stages, each lasting 6 weeks ±14 days, V1–V4 (Table 2). The actual amount of total protein of the allergenic food in the first dose at V1 (Table 2) starts slightly below calculated discrete ED05 values for the correspondent food allergens,^25^ which are 2.1 mg peanut protein, 3.5 mg hazelnut protein, 2.3 mg hen's egg protein, and 2.4 mg cow's milk protein. Further ingredients of the biscuit are wheat flour type 550 and margarine processed with rapeseed oil.

**TABLE 2 pai70147-tbl-0002:** Content of Peanut, Hazelnut, Hen's Egg, and Cow's Milk protein in the ground biscuit.

Group A	Visit 1–Visit 2	Visit 2–Visit 3	Visit 3–Visit 4	Visit 4–Visit 5/6

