Questionnaires Allergy (family members)	x	x										
Medical history, vaccination record	x	x		x		x		x		x		
Review AEs			x	x	x	x	x	x	x	x	x	x
Review concomitant medication	x	x	x	x	x	x	x	x	x	x	x	x
Nutritional characteristics^d^	x	x		x		x		x		x		x
Physical examination	x	x		x		x		x		x	x	x
SCORAD, EASI score		x		x		x		x		x	x	x
Palm lines documentation		x										
TEWL (Berlin)		x		x		x		x		x		
SPT										x		x
Stool scales^d^	x	x		x		x		x		x		
Postnatal hygiene score		x		x		x		x		x		
Pacifier questionnaire		x		x		x		x		x		
Palatability score^d^		x		x		x		x		x		
POEM score (Eczema)		x										
Skin swab infant (cheek)	x	x				x				x		
Skin swab caregiver (cheek)	x	x								x		
Skin swab caregiver (mamilla)	x	x				x				x		
Skin swab infant (body, interscapular)	x	x				x				x		
Oral swab infant		x				x				x		
Oral swab caregiver		x								x		
Stool sample infant	x	x				x				x		
Stool sample caregiver	x	x								x		
Blood draw		x								x	(x)	x
Dental status		X (Caregiver)								X (Child)		
Intervention												
Feeding of SP at site		x		x		x		x				x
Dispensation of SP		x		x		x		x		(x)^a^		x
Review compliance + tolerance of SP			x		x		x		x			x
OFC											x^a^	

Visit/Phone call	Enrolment/Screening		Reference period				V5	V5 solo^c^	(V6)^a^	Unscheduled Visit^b^
	V0 (optional)	V1	PC1		PC2					
(b) *Schedule of Events – Group B*										
Timepoint (week)		0	2 wks after V1		12 wks		24 wks (±14 d)			
Enrolment										
Informed consent	x	x^e^						x		
Check eligibility	x	x^e^						x		
Assessments										
Demographics/subject characteristics	x	x					x	x		x
Family characteristics	x	x					x	x		x
Medication, nutrition, exposure to smoking during pregnancy	x	x						x		
Questionnaires Allergy (family members)	x	x						x		
Medical history, vaccination record	x	x					x	x		x
Review AEs			x		x		x		x	x
Review concomitant medication	x	x	x		x		x	x	x	x
Nutritional characteristics^d^	x	x					x	x		x
Physical examination	x	x					x	x	x	x
SCORAD, EASI score		x					x	x	x	x
Palm lines documentation		x						x		
TEWL (Berlin)		x					x	x		x
SPT							x	x		x
Stool scale^d^	x	x					x	x		
Postnatal hygiene score		x					x	x		
Pacifier questionnaire		x					x	x		
Palatability score^d^		x						x		
POEM score (Eczema)		x						x		
Skin swab infant (cheek)	x	x					x	x		
Skin swab caregiver (cheek)	x	x					x	x		
Skin swab caregiver (mamilla)	x	x					x	x		
Skin swab infant (body, interscapular)	x	x					x	x		
Oral swab infant		x					x	x		
Oral swab caregiver		x					x	x		

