#### Main secondary endpoints (for further endpoints, please see Appendix S1)

2.4.2

Compliance assessment/adherence of parents/caregivers conducting pre‐chewing via questionnaire on performance and frequency: query on a weekly basis, if performed daily; 4–7 times per week; <3 times/week (compliance defined as at least 4 days/week ≙ 57%)Composition of the oral microbiome and frequency of infant caries by 1 year of age (V5) according to the International Caries Detection and Assessment System (ICDAS, a clinical scoring system allowing detection and assessment of caries lesions and caries experience^30^)Frequency of IgE‐mediated food allergies to at least one of the four foods (hen's egg, cow's milk, peanut, hazelnut) after intervention by 1 year of age (V5) between Groups A and BAllergen‐specific IgE and IgG4 to hen's egg, cow's milk, peanut, hazelnut, Ara h 2, Cor a 14, and wheat at V1 and V5 in comparison between groups.Cumulative occurrence (frequency and severity) of respiratory and gastrointestinal infections (including oral infections) in comparison between groups

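### Infections are compared between groups as a cumulative count, but ordinary infections have no stated REDCap entry, site AE reviews number 8 in Group A and 3 in Group B, and follow-up length may differ

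*Protocol article*

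**What the plan says.** Section 2.4.2 of the protocol article lists among the main secondary endpoints: "Cumulative occurrence (frequency and severity) of respiratory and gastrointestinal infections (including oral infections) in comparison between groups". It names no observed-time denominator.

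Section 4.1 (Harms) gives the recording rule: "Any adverse event (AE) will be documented on paper (diary"; then "Adverse events of special interest (AESIs) as well as serious adverse events (SAEs) will also be documented in the Research Electronic Data Capture, REDCap". The AESI list has three entries: immediate-type allergic reactions, recurrent gastrointestinal symptoms or abdominal pain, and new-onset eczema.

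Section 2.3.1 sets the status of the diary: "All caregivers will be encouraged to keep a weekly diary". It is to cover adverse events, concomitant medication and diet as well as feeding.

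Table 3 adds site contacts at which AEs are reviewed, with different calendars for Groups A and B. It also has a row "Review concomitant medication", marked at every call and visit in both groups.

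On the timing of Group B's last visit, section 2.3.1 places V5 near the first birthday, while Table 3(b) gives 24 weeks with a window of 14 days either way. Section 3.3 states that missing values will not be imputed.

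**The concern.** Passing on infection is the main safety question about pre-chewing. The Discussion says so, promises to watch infections closely, and hopes the trial may show that saliva exchange is not harmful in itself. The infection comparison is the endpoint that would carry such a statement.

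An ordinary cold, an oral infection or a single gastroenteritis does not meet the AESI list and will rarely meet an SAE criterion. Section 4.1 therefore gives it no stated route into the electronic record. What is captured depends on how well the diary is kept and how often the site asks. The second differs between groups by design, and the first may differ too. Parents choose the group and nobody is blinded, so nothing offsets unequal detection. A cumulative count also grows with observation time, which the article does not fix consistently for Group B.

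**Working it through.** The article gives no infection rate, effect size or diary completeness, and no sample size calculation was made. There is no figure of the plan's own to reproduce. The check sets the recording rule beside the schedule and then shows how each inequality would act on a raw count.

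**1. AE reviews through V5 (Table 3, row for AE review)**

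| | Contacts | Nominal weeks | Number | Longest gap |
|---|---|---|---|---|
| Group A | PC1, V2, PC2, V3, PC3, V4, PC4, V5 | 2, 6, 8, 12, 14, 18, 20, 24 | 8 | 4 weeks |
| Group B | PC1, PC2, V5 | 2, 12, 24 | 3 | 12 weeks |
| V5 solo | none | – | 0 | – |

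Both groups also have the review at V6 and at unscheduled visits. The shared contacts are weeks 2, 12 and 24. Group A has 8 − 3 = 5 further reviews.

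**2. Observation time**

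Table 3 gives 24 ± 2 weeks, that is 22 to 26, for both groups. The Figure 1 legend puts V1 at 4 to 8 months for Group A. Assume the same for Group B and take 52/12 = 4.33 weeks per month. Time from V1 to the first birthday is then

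- start at 8 months: 4 × 4.33 = 17.3 weeks
- start at 6 months: 6 × 4.33 = 26 weeks
- start at 4 months: 8 × 4.33 = 34.7 weeks.

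With equal weekly infection rates and complete recording, the ratio of mean counts A/B equals the ratio of follow-up times. With 24 weeks in A it is 24/17.3 = 1.38, 24/26 = 0.92 or 24/34.7 = 0.69. The outer values need every Group B infant to start at one end of the range, so they bound the effect and do not predict it.

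**3. Detection (illustration on assumed values)**

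Suppose true rates are equal and a share c of infections reaches the data in each group. The observed ratio is then c_A / c_B.

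- 90% v 90%: 1.00
- 90% v 70%: 0.9/0.7 = 1.29
- 70% v 90%: 0.7/0.9 = 0.78

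Take 50 infants per group, Poisson counts and a two-sided 0.05 test, with 90% v 70%:

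- 2 true infections per child: means 1.8 and 1.4, SE = √(3.2/50) = 0.253, z = 0.4/0.253 = 1.58, chance of a false difference 35%
- 4 true infections per child: means 3.6 and 2.8, SE = √(6.4/50) = 0.358, z = 0.8/0.358 = 2.24, chance of a false difference 61%.

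The capture shares and infection numbers are assumptions. Equal capture leaves the ratio unbiased, though both counts are too low.

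**The case against.** Two stronger readings are tempting, and the documents support neither.

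- A reader might infer that non-serious infections are recorded only in the diary. Table 3 schedules AE reviews in both groups, concomitant medication is reviewed at every contact, and medical history is taken again at later site visits. Recurrent gastrointestinal symptoms are an AESI and will catch some gastrointestinal infections. A family without a diary is still asked.
- A reader might infer that blank diary weeks are scored as infection-free. The article nowhere says so. Section 3.3 rules out imputation, and counting a blank as zero would itself be a form of imputation. However, the rule does not settle the matter: a plain sum adds nothing for an unobserved week unless observed time is defined.

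It can also be said that the article is abridged. Data management and further outcome definitions are in Appendix S1, which is not shown. Section 4.1 does not say that diary entries never reach the database, and the subcohort analyses by infection in section 3.3 suggest that they should. The case definition of an infection and the choice of count model may properly stand elsewhere, and their absence here is no fault.

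On V5 solo, no text says these infants are scored for infections, and they do have medical history and concomitant medication recorded. All analyses other than the primary one are labelled explorative.

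These objections remove the two stronger readings and lower the stakes. They do not touch the unequal AE reviews, the two descriptions of Group B's V5, or a recording rule that names the events for REDCap and leaves out those of a main secondary endpoint.

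**Conclusion.** The point holds in a limited form. As written, the between-group comparison of infections is a cumulative count under documented unequal ascertainment (8 v 3 reviews through V5) and possibly unequal observation time. Ordinary infections have no stated entry in REDCap. The comparison can therefore favour either group with no true difference. More frequent questioning would tend to raise the count in Group A. Diary keeping and follow-up length could act in either direction.

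The size of any bias cannot be derived from the article. The ratios 1.29 and 0.78 rest on assumed capture shares. The range 0.69 to 1.38 rests on Group B starting at 4 to 8 months and ending at the first birthday. The primary microbiome endpoint is not affected. The change should be made because the infection result bears on the trial's main safety question and the remedy is cheap.

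**What to change.** 1. **Recording (section 4.1).** Add respiratory, gastrointestinal and oral infections of the infant to the events entered in REDCap, with date, type and severity. Enter them at contacts already scheduled, together with the diary weeks covered since the last contact.
2. **Equal questioning.** Ask the same structured infection question, with the same look-back period, in both groups at weeks 2, 12 and 24. Base the between-group comparison, or at least a sensitivity analysis, on these contacts. Infections found only at Group A's 5 further reviews can be reported descriptively. The week-12 contact is a visit in A and a call in B, so the question should be scripted.
3. **Analysis (section 2.4.2).** Define the endpoint as infections per observed infant-week, compared by a count model (for example negative binomial) with log observed time as offset. State that weeks without information are unobserved, not zero.
4. **V5 solo.** Leave these infants out of this endpoint.
5. **Timing.** Reconcile the two descriptions of Group B's V5. The offset handles differing lengths whichever is kept.

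The offset alone does not remove bias from unequal questioning, so items 2 and 3 are both needed. It also assumes that infections are no likelier in unobserved weeks.

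The cost is one REDCap form, a short script and analysis wording, with somewhat more data entry per infection. No visit or procedure is added.

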### Study setting

2.1

All visits throughout the study will take place either in the study centres (V1–V5) or on the ward (V0: on the ward of the Division Obstetrics and Prenatal Medicine, Goethe University Frankfurt, Frankfurt am Main, Germany, and V6: on the ward of the Department of Pediatrics, Division of Pneumology, Allergology, Infectious Diseases and Gastroenterology, Goethe University Frankfurt, or of the Department of Pediatric Respiratory Medicine, Immunology and Critical Care Medicine, Charité – Universitätsmedizin Berlin).

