Our biggest concern is that we will not recruit enough caregivers who choose to take part in the pre‐chewing group. Premastication is not well known and is viewed rather critically in Germany.^46^ However, as our primary objective is to analyze whether the transmission of pre‐chewed foods for solid introduction has any influence on the infant's microbiome, we decided to choose an open‐study design despite the various limitations and the bias by the open selection of study groups. As data on the effect of pre‐chewing on microbiome analysis is rare, the estimated power is based on current publications that have in some way addressed the transfer of saliva,^38^ analyzed the oral microbiota in relation to allergy development,^39^ or analyzed its composition after premastication.^37^ Although the open design and the question of power are the biggest limitations, these factors also strengthen the outstanding position of this trial. This study will allow us to not only analyze the changes in microbiome composition (oral, skin, intestinal) over time, but also the influence of premastication for the first time. This exploratory first approach is built up carefully in order to identify danger signals early on. But we can also perhaps show that the exchange of parental saliva on the child is not “harmful” per se, but can also do “good”.

As final remark, it should be emphasized that this open trial will not be suitable for drawing recommendations on the prevention of cow's milk, hen's egg, peanut, and/or hazelnut allergies based on the outlined approach. This is particularly the case since no placebo biscuit (ground biscuit without the four food allergens) with or without pre‐chewing is included. Rather, the practicability and acceptance of the old feeding practice of premastication (if done at all, when and how often it is carried out) and its impact on the infant's microbiome will be assessed. Nevertheless, this study is a first step in pursuing the hypotheses on this combined approach and a potential utilization of premastication as an “allergy‐protective” puzzle piece for food allergy prevention.

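### The SAE definition leaves out emergency-treated allergic reactions that are not judged life-threatening and end in discharge within 24 h, so the 48-hour report does not apply to them

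*Protocol article*

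**What the plan says.** Section 4.1 (Harms) sets out the SAE definition in full. It opens with "An SAE will be defined as any AE that fulfills at least one of the following criteria: results in death". The further criteria are a life-threatening event, one that "requires inpatient hospitalization (longer than 24 h) or prolongation of existing hospitalization", and the closing item, "or results in persistent or significant disability or incapacity". Nothing follows, so the list is closed at four items.

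The reporting clock comes just before: "SAEs have to be reported within 48 h after knowledge of the event to the principal investigator". It is stated for SAEs only.

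Allergic reactions have their own entry among the events of special interest: "Objective immediate‐type allergic reactions within 2 hours of food exposure", whether caused by the study product or by another food. For AESIs in general, "In case of an AESI, caregivers will be strictly advised to contact the study site as soon as possible". For this item the caregiver is also asked to make an emergency call, record the symptoms, and ring the site ahead of any further portion in Group A. AESIs and SAEs both go into REDCap as well as the paper diary.

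The Discussion says the approach was built up carefully "in order to identify danger signals early on".

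**The concern.** The most foreseeable acute harm of this intervention is an allergic reaction. Infants at atopic risk receive four allergenic foods in rising amounts, mostly at home. Section 4.1 itself describes the reaction of interest as immediate, within two hours of exposure. Such a reaction can be serious and still be over within a day. A criterion based on length of stay therefore sorts these events by how long the child was kept in, when what matters is how serious the reaction was.

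Two things are at stake. One is what the SAE count means for this product. The other is whether a reaction that needed emergency care reaches the principal investigator within a stated time, in a trial that aims to see danger signals early.

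**Working it through.** There is no stated figure to reproduce: the article gives no SAE rate, and it says no sample size calculation was done. The check is to apply the four criteria of Section 4.1 to an objective allergic reaction to the biscuit that is neither fatal nor disabling and does not prolong an existing stay.

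| Case | Life-threatening? | Inpatient stay > 24 h? | SAE as written? | 48-hour report? |
|---|---|---|---|---|
| 1. Judged life-threatening, discharged the same day | yes | no | yes | yes |
| 2. Not so judged, admitted for more than 24 h | no | yes | yes | yes |
| 3. Not so judged, emergency treatment, admitted, discharged within 24 h | no | no | **no** | **no** |
| 4. Not so judged, emergency treatment, not admitted | no | no | **no** | **no** |

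Cases 2 and 3 may be the same reaction. Only the time of discharge separates them, yet one is an SAE and the other is not. Cases 3 and 4 meet none of the four criteria.

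What happens to cases 3 and 4 instead:

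- **Onset within 2 hours:** the reaction is an AESI. It is entered in REDCap, the caregiver contacts the site as soon as possible, and the site hears before the next portion.
- **Onset after 2 hours:** the allergic AESI item is not met. Unless another AESI item applies, the stated record is the diary, together with the adverse-event review at phone calls and visits in Table 3.

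Applying a changed definition: deleting the 24 h qualifier brings in case 3 but not case 4, because case 4 involves no admission. A criterion for other medically important events that names emergency-treated allergic reactions brings in case 4. Both changes are needed.

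For exposure only: with 50 infants in Group A, 24 weeks (four steps of 6 weeks) and 4 to 7 portions a week, 50 × 24 × 4 = 4,800 and 50 × 24 × 7 = 8,400 portions. The supervised first portions number 50 × 4 = 200. This shows that most feeding is at home. It says nothing about how often reactions occur.

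**The case against.** The case for leaving the text alone is substantial, and much of it stands.

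- **The harm already has a route.** A reader might infer that severe reactions go unrecorded or that nobody hears of them in time. The document does not support this. Reactions within 2 hours are AESIs in REDCap whatever the length of stay, and the site must be called before re-exposure, which with portions given on at least four days a week may come sooner than 48 h. First portions of each step are observed at the site for two hours. This stands. What remains is that Section 4.1 states no time-bound report to the principal investigator for these events.
- **The gravest reactions are covered.** A reader might infer that the SAE count could stay at zero however severe the reactions. It could not: an event judged life-threatening is an SAE regardless of stay. The gap is the band below that judgement.
- **The AESI items are kept apart.** Allergic reactions, recurrent abdominal symptoms and new eczema are three listed items, each with its own instructions, so they can be reported separately.
- **The infants are not naive to all four foods.** Table 1, footnote a, allows previous cow's milk consumption.
- **Appendix S1 is not shown.** A forwarding deadline or severity grading for AESIs may be set there or in the full protocol, so their absence from the article is no finding. This does not reach the SAE definition, which the article prints in full and does not defer.
- **No internal contradiction.** Nothing in the document requires a medically-important-event criterion. That is true. The objection to the rule is that it fits this product's main acute risk poorly and sits badly with the stated aim of early detection.

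One might also guess that the 24 h limit was meant to keep planned challenge stays out of the SAE list, since V6 takes place "on the ward of the Department of Pediatrics" or its Berlin counterpart. The article gives no length of stay for V6 and does not link it to the SAE rule, so this remains a guess.

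**Conclusion.** The point holds as a flaw in a stated definition. An objective allergic reaction to the biscuit that needs emergency treatment, is not judged life-threatening and ends in discharge within 24 h meets none of the four SAE criteria and does not trigger the 48-hour report. Whether such an event is an SAE then rests on the life-threatening judgement alone.

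The gap is one of classification and of the stated report. It is not a failure of data capture for reactions within 2 hours. The number of affected events cannot be estimated from the document, and the portion count must not be read as a forecast of harm. The conclusion assumes that the SAE list in Section 4.1 is the one in force. The Ethics statement says amendments were added during the trial, so the sponsor should first confirm that none has changed it.

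**What to change.** In Section 4.1, and in the full protocol it condenses:

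1. Delete the words that limit the hospital criterion to stays longer than 24 h.
2. Exempt admissions planned for study procedures, such as V6, so that a scheduled challenge stay does not count by itself.
3. Add a criterion for other medically important events, stating that it includes objective allergic reactions needing emergency medical treatment. Place it on the same 48-hour route to the principal investigator.
4. Reclassify existing REDCap and diary records on this definition before the safety tables are reported. Include the diary, because reactions starting after 2 hours may be recorded only there.

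These changes concern classification and reporting only and leave dosing and treatment untouched. The cost is an amendment to the safety wording, a small change to the REDCap form and one pass through existing records. The downside is that the reported SAE count may rise slightly, so the report should state which definition was applied.
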